## **12.4. Data Queries**

Data arriving at UCL CTC and entered onto the online eCRF database will be checked for completeness, accuracy, legibility and consistency, including checks for missing or unusual values. Data Clarification Requests will be sent / raised for the attention of the data / lead research contact at site. Further guidance on how data contacts should respond to data queries can be found on the Data Clarification Request forms. UCL CTC will send regular reports to sites, listing any overdue forms that require completion. Repeated failure to complete data queries / complete eCRFs within the required timeframes, will result in an escalation procedure that may involve suspension to recruitment at the trial site. Sites should inform UCL CTC ASAP of any issues they may experience that affects the completion of the data required.

## 13. PHARMACOVIGILANCE

### 13.1. Definitions

The following definitions have been adapted from the Medicines for Human Use (Clinical Trials) Regulations 2004 (SI 2004/1031) and subsequent amendments and ICH E2A “Clinical Safety Data Management: Definitions and Standards for Expedited Reporting” and ICH GCP E6.

#### ***Adverse Event (AE)***

Any untoward medical occurrence in a patient treated on a trial protocol, which does not necessarily have a causal relationship with a trial treatment. An AE can therefore be any unfavourable and unintended sign (including an abnormal laboratory finding), symptom or disease temporally associated with the use of a trial treatment, whether or not related to that trial treatment. See section 13.2.1 for AE reporting procedures.

#### ***Adverse Reaction (AR)***

All untoward and unintended responses to a trial treatment related to any dose administered. A causal relationship between a trial treatment and an adverse event is at least a reasonable possibility, i.e. the relationship cannot be ruled out.

#### ***Serious Adverse Event (SAE) or Serious Adverse Reaction (SAR)***

An adverse event or adverse reaction that at any dose:

- Results in death.
- Is life threatening (the term “life-threatening” refers to an event in which the patient was at risk of death at the time of the event. It does not refer to an event that hypothetically might have caused death if it were more severe).
- Requires in-patient hospitalisation or prolongs existing hospitalisation.
- Results in persistent or significant disability/incapacity.
- Is a congenital anomaly or birth defect.
- Is otherwise medically significant (e.g. important medical events that may not be immediately life-threatening or result in death or hospitalisation but may jeopardise the patient or may require intervention to prevent one of the other outcomes listed above).

See section 13.2.2 for SAE reporting procedures.

#### ***Suspected Unexpected Serious Adverse Reaction (SUSAR)***

An adverse event meeting the following criteria:

- Serious – meets one or more of the serious criteria above.
- Related – assessed by the local investigator or sponsor as causally related to one or more elements of the trial treatment.

- Unexpected – the event is not consistent with the applicable reference safety information (RSI).

See section 13.3 for reporting procedures for these events.

### ***Adverse event of special interest (AESI)***

An AE that is of special interest to the Trial Management Group MSD, even if does not meet the standard criteria for seriousness, or it occurs outside the standard AE reporting timeframes for the trial.

See section 13.4 for reporting procedures for these events.

## **13.2. Reporting Procedures**

### ***Adverse Event Term***

An adverse event term must be provided for each adverse event. Wherever possible a valid term listed in the Common Terminology Criteria for Adverse Events (CTCAE) v5 should be used. This is available online at:

[https://ctep.cancer.gov/protocoldevelopment/electronic\\_applications/ctc.htm#ctc\\_50](https://ctep.cancer.gov/protocoldevelopment/electronic_applications/ctc.htm#ctc_50)

### ***Severity grade***

Severity grade of each adverse event must be determined by using CTCAE v5.

### ***Causality***

The relationship between the treatment and an adverse event will be assessed.

For AEs, the local PI or designee will assess whether the event is causally related to trial treatment.

For SAEs, a review will also be carried out by the Sponsor's delegate.

Causal relationship to trial treatment must be determined as follows:

- Related (reasonable possibility) to a trial treatment
- Not related (no reasonable possibility) to a trial treatment

UCL CTC will consider events evaluated as related to be adverse reactions.

### **13.2.1. Reporting of Adverse Events (AEs)**

For registered patients who have received treatment, all adverse events that occur between informed consent and 30 days (or 110 for AESIs) post last trial treatment administration (see section 17.1 for end of trial definition) must be recorded in the patient notes and the trial eCRFs. Those meeting the definition of a Serious Adverse Event

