**Dose modifications are not permitted.**

#### **9.5. Management of Adverse Events**

AEs associated with pembrolizumab exposure may represent an immunologic etiology. These immune-related AEs (irAEs) may occur shortly after the first dose or several months after the last dose of pembrolizumab treatment and may affect more than one body system simultaneously. Therefore, early recognition and initiation of treatment is critical to reduce complications. Based on existing clinical study data, most irAEs were reversible and could be managed with interruptions of pembrolizumab, administration of corticosteroids and/or other supportive care. For suspected irAEs, ensure adequate evaluation to confirm etiology or exclude other causes. Additional procedures or tests such as bronchoscopy, endoscopy, skin biopsy may be included as part of the evaluation. Based on the severity of irAEs, withhold or permanently discontinue pembrolizumab and administer corticosteroids. Dose management guidelines for irAEs associated with pembrolizumab are provided in Table 4.

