    - In hyperthyroidism, non-selective beta-blockers (e.g. propranolol) are suggested as initial therapy.
    - In hypothyroidism, thyroid hormone replacement therapy, with levothyroxine or liothyronine, is indicated per standard of care.

- **Grade 3-4** hyperthyroidism:
  - Treat with an initial dose of IV corticosteroid followed by oral corticosteroids. When symptoms improve to Grade 1 or less, steroid taper should be started and continued over no less than 4 weeks. Replacement of appropriate hormones may be required as the steroid dose is tapered.
- **Hepatic:**
  - For **Grade 2** events, monitor liver function tests more frequently until returned to baseline values (consider weekly).
    - Treat with IV or oral corticosteroids
  - For **Grade 3-4** events, treat with intravenous corticosteroids for 24 to 48 hours.
  - When symptoms improve to Grade 1 or less, a steroid taper should be started and continued over no less than 4 weeks.
- **Renal Failure or Nephritis:**
  - For **Grade 2** events, treat with corticosteroids.
  - For **Grade 3-4** events, treat with systemic corticosteroids.
  - When symptoms improve to Grade 1 or less, steroid taper should be started and continued over no less than 4 weeks.
- **Stevens-Johnson syndrome (SJS) and toxic epidermal necrolysis (TEN):**

Cases of SJS and TEN, some with fatal outcome, have been reported in patients treated with pembrolizumab. For signs or symptoms of SJS or TEN, withhold pembrolizumab and refer the patient for specialised care for assessment and treatment. If SJS or TEN is confirmed, permanently discontinue pembrolizumab.
- **Other important potential risks include:** Based upon additional information received from the clinical study and postmarketing environments immune-mediated ADRs may be fatal and may occur after discontinuation of pembrolizumab.
- Arthritis adverse reactions have been identified during post-approval use of pembrolizumab. As these reactions are reported voluntarily from a population of uncertain size, it is not always possible to reliably estimate their frequency or establish a causal relationship to drug exposure.
- Immune-mediated irARs such as myocarditis, adrenal insufficiency, thyroiditis, uveitis, cholangitis, myositis, encephalitis and lung disease may occur. If a patient experiences any of these events, consult relevant medical specialists for management as per local policies.

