### 10.2.1. Adverse Event (AE) Monitoring

The investigator or qualified designee will assess each patient to evaluate for potential new or worsening AEs and more frequently if clinically indicated. AEs will be graded and recorded throughout the study and during the follow-up period according to NCI CTCAE Version 5. AEs will be characterised in terms regarding seriousness, causality, grading, and action taken with regard to trial treatment.

Please refer to Section 13.2 for detailed information regarding the assessment and recording of AEs.

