## 10.6. Assessments During Follow Up (before progression)

Patients will have post-treatment follow-up for disease status, until disease progression, death, withdrawing consent, or becoming lost to follow-up.

These patients who discontinue trial treatment for a reason other than disease progression should be assessed **every 12 weeks** ( $84 \pm 7$  days), following the end of treatment, by radiologic imaging to monitor disease status. Every effort should be made to collect information regarding disease status until disease progression, death, end of the study or if the patient begins re-treatment with pembrolizumab as detailed in Section 9.3.3. Information regarding post-study anti-cancer treatment will be collected if new treatment is initiated.

Patients who are eligible and have consented to receive re-treatment with pembrolizumab according to the criteria in Section 9.3.3 will move from the follow-up phase to the re-treatment period when they experience disease progression.

Assessments to be completed during follow-up are:

- **Adverse Events review** as per requirements detailed in the pharmacovigilance sections 13.2.1 (AE), 13.2.2 (SAE) and 13.4 (AESI)
- **CT scan of chest, assessable by RECIST v1.1**
- **CT scan or MRI scan** assessable by RECIST v1.1) (abdomen, pelvis, and brain (if patient assessed with brain metastases at baseline)
- **Additional anti-cancer treatment review**
- **Survival status**
- **QoL: FACT-O**
- **Biopsy** (if first disease progression on the trial during the follow-up period has been confirmed) – should be performed within 6 weeks\*.

\*In the event of any local covid-19 restrictions impacting resource at site to perform the biopsy as scheduled, the biopsy may be performed at a later timepoint, if it becomes possible and safe to do so later on, and as long as the patient has not proceeded with further cancer treatment Site must contact the CTC prior to this been re-arranged for approval from the CI/TMG.

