### 13.2.2. Reporting of Serious Adverse Events (SAEs)

For registered patients who have received treatment, all SAEs that occur between the signing of informed consent and 110 days post last trial treatment administration (**or after this date if the site investigator feels the event is related to a trial treatment**) must be submitted to UCL CTC by fax / email within **24 hours** of observing or learning of the event, using the trial specific SAE Report. All sections on the SAE Report must be completed. If the event is **not being reported within 24 hours** to UCL CTC, the circumstances that led to this must be detailed in the SAE Report to avoid unnecessary queries.

For consented patients in screening and not registered to the trial or have been registered but not yet started trial treatment, those SAEs that occur between the signing of informed consent and 14 days post the last trial screening test must be submitted to UCL CTC by fax / email within 24 hours of observing or learning of the event, using the trial specific SAE Report.

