|                           | 
a = Pre-existing conditions prior to start of treatment are added as medical history data, any conditions that worsen after treatment then require reporting as an AE.
 
b = Pregnancy testing required within 3 days prior to registration.
 
c = Pre-cycle 1, day 1 treatment bloods to be performed within 10 days prior to registration i.e. they do not need to be repeated following baseline for day 1 cycle 1.
 
d = Ca125 to be performed within 14 days prior to registration.
 
e = Re-biopsy 6-8 weeks during treatment and upon progression.
 
f = exploratory bloods at cycles 2, 4 & 6, then at 12 months only.
 
g = At the time of disease progression.
 
h = AEs 30 days post last treatment, SAEs up until 110 days post last treatment and longer if a late term SAR, and AESIs up until 110 days post treatment.
 
i = Archival tissue collected.
 
j = If patient has not progressed, imaging, CA125 and QoL continues until progression.
 
K = Baseline exploratory bloods can also be taken after registration and pre cycle 1 day 1, if logistically more suitable to take at that time.
 
L= Imaging & QoL every 12 weeks until end of treatment (also see code J).
 |                                                                 |                                                                                                           |   |   |   |   |   |   |   |   |                                              |                                            |                                     |

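### Non-serious immune-related adverse events that start more than 30 days after the last dose need not be recorded unless they meet the narrow AESI definition, although section 9.5 expects such events months later

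*Protocol*

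**What the plan says.** The protocol sets tiered recording windows after the last dose.

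- **Ordinary adverse events.** Section 13.2.1 covers "all adverse events that occur between informed consent and 30 days (or 110 for AESIs) post last trial treatment administration".
- **Serious events.** Section 13.2.2 covers "all SAEs that occur between the signing of informed consent and 110 days post last trial treatment administration", and later events too if the investigator considers them related.
- **Schedule.** Appendix 1, footnote h, repeats the tiers: "AEs 30 days post last treatment, SAEs up until 110 days post last treatment and longer if a late term SAR", with AESIs also to 110 days.
- **AESIs.** Section 13.4 lists two: overdose, and a pattern of raised AST or ALT with raised bilirubin and alkaline phosphatase below twice the upper limit of normal.

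On timing, section 9.5 says immune-related events "may occur shortly after the first dose or several months after the last dose of pembrolizumab treatment". The text after Table 4 adds that "immune-mediated ADRs may be fatal and may occur after discontinuation of pembrolizumab".

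Two other sections bear on the recording period. Section 10.2.1 says "AEs will be graded and recorded throughout the study and during the follow-up period according to NCI CTCAE Version 5". Section 10.5 asks for all adverse events in the period up to the end-of-treatment visit, which is set at 30 ± 7 days from the last dose or from the decision to stop. Safety is a secondary objective (4.1.2), and 18.2.2.7 reports event frequencies and the worst event per patient.

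**The concern.** The window for ordinary events is shorter than the time course that the protocol itself describes for immune-related toxicity, and the AESI exception is too narrow to close the gap. Non-serious colitis, hypothyroidism, rash or arthritis that starts on day 60 after the last dose falls outside every required tier.

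The treatment given for it would not reveal it either. Under section 9.8.1, concomitant medication more than 30 days after the last dose is recorded only for SAEs and AESIs.

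At stake is the completeness of the late, non-serious part of the safety profile. Section 13.5 also relies on recorded events to detect new reactions and rare events that are more frequent than the Investigator's Brochure states. A secondary risk is that sites stop recording at different times, because 10.2.1, 10.5 and 13.2.1 do not describe the same period.

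**Working it through.** The plan computes no figure on this point. The check compares the stated windows.

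**1. Required recording after the last dose**

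| Event type | Recorded until | Source |
|---|---|---|
| Serious | day 110; no end date if judged related | 13.2.2, footnote h |
| AESI (overdose, one liver-test pattern) | day 110 | 13.2.1, 13.4, footnote h |
| Any other non-serious event, including immune-related | day 30 | 13.2.1, footnote h |

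**2. Length of the gap**

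110 − 30 = 80 days (80 / 7 = 11.4 weeks), and 80 / 110 = 73% of the post-dose period in which sites must already look for serious events. This is a share of days, not of events.

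**3. Direction and size**

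Leaving events out can only lower a frequency or a worst-event summary, so the direction is fixed. The size is not, because the protocol gives no rate of late non-serious immune-related events. Purely as an assumption, let a proportion *s* of 48 patients have such an event between days 31 and 110. The number of patients with an unrecorded event is 48 × *s*:

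| *s* | Patients |
|---|---|
| 2% | 1.0 |
| 5% | 2.4 |
| 10% | 4.8 |
| 20% | 9.6 |

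The effect on the worst-event summary would be smaller, because some of these patients will already have a recorded event at least as severe.

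**4. Section 10.5 against 13.2.1**

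- Visit timed from the last dose: 30 ± 7 gives days 23 to 37, so it can pass day 30 by a week.
- Visit timed from a decision to stop one 3-week cycle after the last dose: 21 + 30 = day 51, range 44 to 58.
- Visit timed from a decision after withheld treatment: Table 4 allows up to 12 weeks (84 days) from the last dose before permanent discontinuation. Then 84 + 30 = day 114, range 107 to 121.

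In the last case the patient keeps attending, because 10.4.2.2 requires the full pre-cycle assessments at visits without drug, and 10.2 includes adverse event review among them. If treatment is never resumed, 13.2.1 read literally ends required recording 30 days after a dose that lies well in the past, while 10.5 asks for events up to the visit.

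**5. Whether existing contacts can carry a longer window**

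The end-of-treatment visit reviews adverse events. So do the 12-weekly follow-up visit (10.6) and the 12-weekly survival call (10.6.1). Under Appendix 1 the first of these contacts is 84 ± 7 days after discontinuation, that is, days 77 to 91. With discontinuation one cycle after the last dose it falls on days 98 to 112 after that dose. Sites must already look for serious events to day 110, so no new contact is needed.

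**The case against.** The strongest case on the other side has four parts.

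- **The windows are consistent where it counts.** Section 10.2.1 sits under assessments during treatment and ends "Please refer to Section 13.2 for detailed information regarding the assessment and recording of AEs". Sections 10.6, 10.6.1 and footnote h all apply the section 13 windows. This stands: a reader might infer that 10.2.1 sets a rival rule that some sites will follow, but its own cross-reference leads back to the 30-day limit. What remains there is loose wording. Section 10.5 is the more concrete mismatch, because it attaches its own period to a visit that can fall well past day 30.
- **Most of the toxicity is captured.** A reader might infer that the drug's characteristic toxicity as a whole is undercounted. The protocol does not support that. Events of all grades are recorded through up to two years of treatment and any re-treatment. Serious events run to day 110, and without limit if related. The definition of serious in 13.1 includes medically significant events, so some late immune-related events qualify.
- **No bias can be sized.** It is tempting to size the loss from the number of patients expected to progress by the week-6 scan. That fails, because 16.1.2 lets treatment continue after unconfirmed progression, and days without recording are not events missed.
- **A frequency labelled with its window is not biased.** The passage in 9.5 is a clinical warning, and a statistical analysis plan could state the window. This is fair, and labelling is the minimum remedy. It makes the summary honest but does not recover the late events.

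**Conclusion.** The point holds in a narrow form. Non-serious, non-AESI immune-related events that start more than 30 days after the last dose are not required to be recorded, although the protocol says such events may appear months later. For them, 80 of the 110 days already monitored for serious events (73%) are empty, and the summaries in 18.2.2.7 can only be understated in that respect. This rests on the stated windows alone and needs no hazard or event-rate assumption. The number of events lost cannot be derived from the protocol; the figures for 2% to 20% of patients are illustrations. The mismatch between 10.5 and 13.2.1 is real, and that in 10.2.1 is one of wording. The primary endpoint and the sample size of 48 are not affected. This is a cheap improvement to a secondary objective, not a flaw that threatens the trial.

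**What to change.** - In 13.2.1 and footnote h, require immune-related adverse events of any grade on the eCRF to 110 days after the last dose, or to the start of new anticancer therapy if earlier. Leave other non-serious events at 30 days.
- Use the end-of-treatment visit and the existing 12-weekly visit or call, with no added tests.
- Reconcile 10.2.1 and 10.5 with 13.2.1, so that one period applies, including when the end-of-treatment visit is timed from the decision to stop or follows a period of withheld treatment.
- In 18.2.2.7, report immune-related events with onset after day 30 separately, and state that the frequencies of other non-serious events cover only the period to day 30.

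The cost is protocol and eCRF wording and some extra data entry. Late events will be less certainly attributable to the drug. They will also be less completely ascertained, because routine laboratory safety tests stop at the end-of-treatment visit and contact after progression is by telephone. A laboratory-only finding such as mild hypothyroidism may still be missed. Stopping at new anticancer therapy shortens the gain in patients who move on early.

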## PEACOC

---

(SAE) must also be reported to UCL CTC using the trial specific SAE Report. Also refer to section 13.2.2 (Reporting of Serious Adverse Events (SAEs)).

Pre-existing conditions (i.e. conditions present at informed consent) do not qualify as adverse events unless they worsen or recur (i.e. improves/resolves and then worsens/reappears again). For example, an AE could be an exacerbation of a chronic or intermittent pre-existing condition including either an increase in frequency and/or intensity of the condition (worsening of the event). Another example of an AE is when a pre-existing condition improves during the trial (e.g. from grade 3 to grade 1) and then it worsens again (e.g. from grade 1 to grade 2), even if the event is of severity equal or lower than the original condition (improvement and recurrence of the event).

**N.B.** the cancer under study and its anticipated day-to-day fluctuations would not be an AE.

### 13.2.2. Reporting of Serious Adverse Events (SAEs)

For registered patients who have received treatment, all SAEs that occur between the signing of informed consent and 110 days post last trial treatment administration (**or after this date if the site investigator feels the event is related to a trial treatment**) must be submitted to UCL CTC by fax / email within **24 hours** of observing or learning of the event, using the trial specific SAE Report. All sections on the SAE Report must be completed. If the event is **not being reported within 24 hours** to UCL CTC, the circumstances that led to this must be detailed in the SAE Report to avoid unnecessary queries.

For consented patients in screening and not registered to the trial or have been registered but not yet started trial treatment, those SAEs that occur between the signing of informed consent and 14 days post the last trial screening test must be submitted to UCL CTC by fax / email within 24 hours of observing or learning of the event, using the trial specific SAE Report.

